## Abstract

**Background:**

The clinical burden of Long COVID, myalgic encephalomyelitis/chronic fatigue syndrome (ME/CFS), and other post-infectious fatiguing illnesses (PIFI) is increasing. There is a critical need to advance understanding of the effectiveness and sustainability of innovative approaches to clinical care of patients having these conditions.

**Methods:**

We aim to assess the effectiveness of a Long COVID and Fatiguing Illness Recovery Program (LC&FIRP) in a two-arm, single-blind, pragmatic, quality improvement, professional cluster, randomized controlled trial in which 20 consenting clinicians across primary care clinics in a Federally Qualified Health Center system in San Diego, CA, will be randomized at a ratio of 1:1 to either participate in (1) weekly multi-disciplinary team-based case consultation and peer-to-peer sharing of emerging best practices (i.e., teleECHO (Extension for Community Healthcare Outcomes)) with monthly interactive webinars and quarterly short courses or (2) monthly interactive webinars and quarterly short courses alone (a control group); 856 patients will be assigned to participating clinicians (42 patients per clinician). Patient outcomes will be evaluated according to the study arm of their respective clinicians. Quantitative and qualitative outcomes will be measured at 3- and 6-months post-baseline for clinicians and every 3-months post assignment to a participating clinician for patients. The primary patient outcome is change in physical function measured using the Patient-Reported Outcomes Measurement Information System (PROMIS)-29. Analyses of differences in outcomes at both the patient and clinician levels will include a linear mixed model to compare change in outcomes from baseline to each post-baseline assessment between the randomized study arms. A concurrent prospective cohort study will compare the LC&FIRP patient population to the population enrolled in a university health system. Longitudinal data analysis approaches will allow us to examine differences in outcomes between cohorts.

**Discussion:**

We hypothesize that weekly teleECHO sessions with monthly interactive webinars and quarterly short courses will significantly improve clinician- and patient-level outcomes compared to the control group. This study will provide much needed evidence on the effectiveness of a technology-enabled multi-disciplinary team-based care model for the management of Long COVID, ME/CFS, and other PIFI within a federally qualified health center.

**Trial registration:**

ClinicalTrials.gov, NCT05167227. Registered on December 22, 2021.

**Supplementary Information:**

The online version contains supplementary material available at 10.1186/s13063-023-07550-3.

## Background

The clinical presentation, severity, and outcomes of coronavirus disease 2019 (COVID-19), which is caused by severe acute respiratory syndrome coronavirus 2 (SARS-CoV-2), are highly heterogeneous [1]. While some patients recover quickly, others suffer from persistent symptoms collectively known as Post-COVID Conditions (PCC) or Long COVID, which could be identified as early as 4 weeks after infection [2]. At present, scientific understanding of the diagnoses, phenotypes, and epidemiology of PCC is evolving [3, 4]. The number of patients experiencing PCC is increasing as acute COVID cases continue to rise as new variants occur and the public decreases prevention activities and behaviors. Many patients are presenting in primary clinics with a wide range of health consequences that are present four or more weeks after infection of SARS-CoV-2. In many patients, the reported persistent symptoms are highly debilitating, whether they arise secondary to detectable organ system damage or are of unclear etiopathogenesis [5]. Several of the most commonly reported persisting symptoms of PCC are also typically present in patients diagnosed with myalgic encephalomyelitis/chronic fatigue syndrome (ME/CFS) and other post-infectious fatiguing illnesses (PIFI) [6]. These include fatigue, post-exertional malaise, and cognitive impairment, among others. Disability resulting from PCC is now covered under the Americans with Disabilities Act [7]. Given clinical similarities in the constellation of symptoms between ME/CFS and PCC, the current clinical knowledge of ME/CFS has been beneficial in the approach to management and care of patients with PCC. Similarly, approaches to improving the clinical care of patients with PCC may also provide insights into the management ME/CFS and other PIFI. Taken together, there is a critical need to advance understanding of the effectiveness and sustainability of innovative approaches to the clinical care of PCC, ME/CFS, and other PIFI.

One potential approach is to utilize a technology-enabled multi-disciplinary team-based care model centered on case consultation and peer-to-peer sharing of emerging best practices (i.e., teleECHO (Extension for Community Healthcare Outcomes)) to support the management of complex cases associated with PCC, ME/CFS, and other PIFI. The teleECHO approach has previously been used in the management of Hepatitis C and HIV infections, and it has expanded into a wide variety of health care contexts^.^ [8, 9]. A typical teleECHO session includes a clinician presenting de-identified patient cases to specialists who then mentor the presenting clinician and others as they learn to manage patients with complex conditions [10]. These case-based discussions are often supplemented with short didactic presentations to improve content knowledge and share evidence-based practices [11]. An important goal of a teleECHO program is to provide primary care providers access to medical experts from a variety of domains who commit to long-term support and engagement in immediate synchronous interactions. Given that this approach is case-based, interactive, and occurs in real-time, it has a set of distinct advantages to the traditional practice of sequential in-person specialty referrals (e.g., cardiology, pulmonology, and neurology) to address complex cases. This may be particularly helpful for cases in which the etiopathogenesis of PCC, ME/CFS, and other PIFI is unclear and evolving, as multiple specialist perspectives may be generated and discussed with the treating primary care clinician. In contrast, the emerging archetype of brick-and-mortar PCC clinics includes a combination of referrals to specialties (e.g., infectious disease, neurology, cardiology, nephrology) that are typically out of reach in low-resource, community-based primary care settings where the majority of high-risk patients will be treated [12–14].

Although teleECHO represents a potentially promising approach to enhancing the complex care of patients, empirical evidence on the effectiveness of this approach to improve patient and clinician outcomes is limited. TeleECHO programs have rarely been evaluated for both effectiveness and implementation outcomes, and evaluations often lack (1) use of randomization, (2) inclusion of both quantitative and qualitative patient- and clinician-level outcomes, and (3) multiple, well-characterized comparison groups (i.e., counterfactuals) [15, 16]. Thus, there remains a need to generate high-quality evidence that a teleECHO program can effectively enhance the management of complex cases associated with PCC, ME/CFS, and other PIFI while maintaining a high-level of sustainability within a community-based primary care setting.

### Objective

The primary objective of the present research is to determine the effectiveness of FHCSD’s Long COVID and Fatiguing Illness Recovery Program (LC&FIRP) on clinician- and patient-level outcomes. LC&FIRP is comprised of a teleECHO program focused on multi-specialty case consultation and peer-to-peer sharing of emerging best practices to support management of complex cases associated with PCC, ME/CFS, and other PIFI. Our secondary objective is to determine the feasibility, acceptability, and sustainability of LC&FIRP. This study is intended to provide a fuller understanding of the potential impact of innovative technology-enabled multi-disciplinary team-based care models in low-resource, community-based primary care settings.

## Methods

The SPIRIT reporting guidelines were used in the development of this protocol [17]. The completed SPIRIT figure for this protocol can also be found in Table 1 for clinicians and patients. No committees have been created or engaged in this trial. Multiple principal investigators JG and CR are responsible for all aspects of the trial. They oversee staff engaged in recruitment, data collection, management, and analysis. Any required and unplanned protocol amendments will be reported to the Institutional Review Board (IRB) and updated in the trial registration.

**Table 1 Tab1:** The overview of the study period including primary care provider (PCP) schedule of enrollment, interventions, and assessments

	**Study period**									
	**Enrollment**	**Allocation**	**Post-allocation**							**Close-out**
**Timepoint**	**0**	**0**	***3 M***	***6 M***	***9 M***	***12 M***	***18 M***	***24 M***	***30 M***	** ≤ *****37 M***
**Clinician enrollment:**										
**Eligibility screen**	X									
***Informed consent***	X									
**Allocation**		X								
***Patient enrollment:***										
***Eligibility***	x									
**Broad Consent**	x									
**Allocation**		x								
**Interventions:**										
***[Intervention A]***			X	X	X	X	X	X	X	
***Patients A***			x	x	x	x	x	x		
***[Intervention B]***			X	X	X	X	X	X	X	
***Patients B***			x	x	x	x	x	x		
**Assessments:**										
***PCP baseline survey***	X									
***PCP follow-up survey***			X	X	X	X	X	X	X	X
***PCP interviews***										X
***Patient baseline survey***	x									
***Patient follow-up survey***			x	x	x	x				

### Study design

We will evaluate LC&FIRP using an effectiveness implementation hybrid type 2 design [16]. Specifically, we will conduct a two-arm, single-blind, pragmatic, quality improvement, professional cluster, randomized controlled trial in which 20 consenting clinicians across primary care clinics at FHCSD will be randomized at a ratio of 1:1 to either participate in (1) weekly teleECHO sessions with monthly interactive webinars and quarterly short courses or (2) monthly interactive webinars and quarterly short courses alone (a control group). All clinicians will have the option to receive Continuing Medical Education (CME) credit for the weekly teleECHO sessions and monthly interactive webinar. More details on the content of the weekly teleECHO sessions, monthly interactive webinars, and quarterly short courses are provided below. Clinicians will participate in LC&FIRP up to 37 months and throughout participation, 856 FHCSD patients diagnosed with PCC, ME/CFS, or other PIFI will be assigned to the participating clinicians (approximately 42 patients per clinician). Patient outcomes will be evaluated according to the study arm of their respective clinicians. Quantitative and qualitative outcomes will be measured at 3-, 6-, 9-,12-, 18-, 24-, and 30-months post-baseline for clinicians and for patients at 3-, 6-, 9-, and 12-months post assignment to a participating clinician. We will concurrently conduct a prospective cohort study to compare the two patient populations resulting from the randomized controlled trial with a third patient population resulting from enrollment at University of Washington’s Post-COVID Rehabilitation and Recovery Clinic (https://www.uwmedicine.org/specialties/post-covid-rehabilitation). An overview of the study period for clinicians and patients can be found in Table 1.

### Setting

Funded by the US Department of Health and Human Services’ Health Resources and Services Administration, Federally Qualified Health Centers (FQHCs) across the USA are responsible for providing health care services to low-income populations [18]. Over 30 million Americans (1 in 3 people in poverty and 1 in 7 people who belong to a racial or ethnic minority group) receive medical care at an FQHC [18]. FHCSD is one of the ten largest FQHC health systems in the nation and provides medical care to more than 165,000 patients through more than 1 million visits annually. The vast majority of FHCSD patients are low-income and are members of a minority population: 87% live below 200% of the federal poverty level, 16% are homeless, 41% are uninsured, and 83% are racial or ethnic minorities, with Black and Latino patients comprising 9% and 59% of the patient population, respectively (both overrepresented relative to San Diego Country demographics).

FHCSD operates 58 sites throughout San Diego, including 22 primary care clinics that are located in federally designated Health Professional Shortage Areas, 18 behavioral health facilities, 2 mobile counseling centers, 8 dental clinics, 3 vision clinics, 2 outpatient and 13 integrated substances use disorder clinics, 3 medication assisted treatment sites, 3 homeless service centers, and a safety net pharmacy. When the first cases of COVID-19 were diagnosed in San Diego County, FHCSD quickly expanded in-house high complexity laboratory capabilities and deployed reverse transcription polymerase chain reaction (RT-PCR) testing for SARS-CoV-2 RNA with Food and Drug Administration emergency use authorization.

FHCSD has also fully deployed a nationally certified Electronic Health Record (EHR) systemwide, which allows for patient portal access and robust clinical outcomes tracking [19, 20]. It is linked with the FHCSD health system’s self-designed, web-based Clinical Management Information System (CMIS), which facilitates patient care processes, quality assurance, and evaluation functions. Because FHCSD’s systems were developed on a service-oriented architecture, they are highly adaptive to meeting FHCSD’s data collection requirements for clinic management and practice analysis and are uniquely able to add new services in a timely fashion. All of the FHCSD health system’s information technology infrastructure is located in a secure data center supported by a diverse broadband network (100–500 mbps) mostly comprised of Cisco network elements. The data center infrastructure is provided with virtual servers and/or high availability services to ensure availability of the systems on a five nines basis. All applications and data are scheduled for backup nightly (full and incremental) and supported by a robust business continuity plan. The EHR system at FHCSD includes SNOMED CT (Systematized Nomenclature of Medicine—Clinical Terms), as the basis of diagnosing. This is then cross-walked to International Classification of Diseases Tenth Revision (ICD-10) and used for administrative coding and for patients’ problem list. The problem list contains all problems (active, non-active) which are managed by the FHCSD health system’s providers. Importantly, an ICD-10 code for PCC has been implemented and FHCSD medical leadership has directed all providers to use the code to identify COVID-19 patients with symptoms lasting for more than 28 days.

Among low-income populations to date, there has been a concerning imbalance between the high incidence, morbidity, and mortality from COVID-19 (and other diseases) and the limited access to healthcare innovations and research. This has highlighted a long-standing and often disregarded problem characterized by underrepresentation of low-income and minority populations in biomedical research and a lack of readily available infrastructure to truly strengthen inclusion in research [21]. If this is not addressed through meaningful effort, then the safety, effectiveness, and sustainability of interventions and treatments derived from research that includes predominately privileged populations will likely have diminished benefits for low-income populations. Rigorous and just scientific research requires significant participation from all without undue burden or exclusion. The present research seeks to address this issue.

#### Participants

The target for weekly teleECHO sessions, monthly interactive webinars, and quarterly short courses is licensed health care professionals. Therefore, the present research will include professional clusters that will consist of primary care physicians, physician assistants, and nurse practitioners at FHCSD caring for patients who have had persistent symptoms and a decline in health-related quality of life associated with PCC, ME/CFS, and/or other PIFI. A total of 20 clinicians (10 in each study arm) will be enrolled and throughout participation, 856 FHCSD patients diagnosed with PCC, ME/CFS, or other PIFI will be assigned to those participating clinicians (42 patients per clinician). In order to achieve a similarly sized sample of patients among cohorts in the proposed longitudinal cohort study, we will include 428 patients from the UW Medicine’s Post-COVID Telehealth Clinic who have been diagnosed with PCC, ME/CFS, and/or other PIFI.

#### Inclusion criteria

Inclusion criteria for clinicians includes (1) being employed by FHCSD for clinical care delivery, (2) being a licensed primary care physician, physician assistant, or nurse practitioner, (3) being willing and able to care for patients who have had persistent symptoms and a decline in health-related quality of life associated with PCC, ME/CFS, and/or other PIFI, and (4) being willing and able to actively participate in LC&FIRP for up to 37 months.

Patients will be referred to LC&FIRP and assigned to a participating clinician if they (1) are 18 years or older, (2) have had persistent symptoms and a decline in health-related quality of life associated with PCC, ME/CFS, and/or other PIFI, and (3) have completed FHCSD’s Broad Consent and authorized their Protected Health Information to be used for research purposes. FHCSD Primary Care Providers use CDC guidelines to diagnosis patients with PCC, ME/CFS, and or other PIFI before referring them to LC&FIRP [22, 23].

#### Exclusion criteria

There are no exclusion criteria.

### Recruitment, enrollment, and study duration

FHCSD medical leadership will send an email invitation for optional participation in LC&FIRP to the approximately 200 eligible clinicians at FHCSD. Those who are interested and meet inclusion criteria will provide written informed consent, complete a baseline survey, and will be randomized to one of the two study arms. Study enrollment commences upon randomization. The duration of the study for clinicians is up to 37 months. Patients assigned to participating clinicians are expected to be engaged in LC&FIRP as directed by their clinician over the course of 12 months.

FHCSD patients who have had persistent symptoms and a decline in health-related quality of life associated with PCC, ME/CFS, and/or other PIFI may be referred to LC&FIRP by a participating clinician or by a non-participating clinician. Patients who take part in LC&FIRP will fall into one of the following four categories: (1) existing and new ICD-10 diagnosis of PCC and a laboratory confirmed SARS-CoV-2 infection, (2) existing and new ICD-10 diagnosis of PCC and no laboratory confirmed SARS-CoV-2 infection, (3) existing and new ICD-10 diagnosis of ME/CFS, and (4) other PIFI. Only those patients who have completed FHCSD’s Broad Consent and authorized their Protected Health Information to be used for research purposes will be allowed to take part in LC&FIRP. Once FHCSD patients are enrolled into the program they will be followed by participating clinicians for a minimum of 1 year. Patients who advise that they have moved out of San Diego County but remain in the state of California may choose to continue seeing their LC&FIRP primary care provider via telehealth appointments and participate in surveys. Patients who have moved out of the state of California may no longer see their assigned LC&FIRP primary care provider due to telehealth laws, but they may choose to continue participating in surveys.

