### Randomization, allocation concealment, and blinding

After eligibility and consent are confirmed and a baseline survey is completed, participating clinicians will be randomized at a ratio of 1:1 to one of the two study arms. An electronic randomization list will be generated using the latest version of the statistical software platform R (version 3.3.2, http://www.r-project.org). The list will be securely integrated into the cloud-based Research Electronic Data Capture (REDCap) tool. Allocation will be concealed from all investigators and staff until the study group is assigned. Only the study manager and research assistants involved in the delivery of the intervention components will subsequently be made aware of allocation. It is not possible to mask participating clinicians; however, their patients will have no knowledge of their potential participation in weekly teleECHO sessions, monthly interactive webinars, and quarterly short courses. All staff who are involved in the collection of data and investigators who conduct analyses will remain blinded to allocation throughout the study.

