#### Patients

Upon assignment to a participating clinician participant, patients will be asked to share current demographic characteristics, symptoms, medical history, health history, and, if applicable, their initial acute COVID-19 experience. Patients will be asked to complete a variety of widely used and validated patient reported outcome surveys that will take an average of 30 min to complete and will be repeatedly collected at 3-, 6-, 9-, and 12-months. In addition, symptom history and, if applicable, initial acute COVID-19 experience questions will be repeated during quarterly surveys to measure any changes over the 12-month follow-up period. Given the diverse nature of symptomatology, the patient cohort will first be characterized using descriptive statistics on domains of dysfunction (e.g., neurologic, cardiac, pulmonary, mental health). Surveys will include (1) Patient-Reported Outcomes Measurement Information System (PROMIS)-29, (2) Health Assessment Questionnaire (HAQ), (3) PROMIS Dyspnea Functional Limitations Short Forms, (4) PROMIS Applied Cognition Abilities and General Concerns Short Forms, (5) Patient Health Questionnaire (PHQ-9), (6)Generalized Anxiety Disorder (GAD)-7, (7) self-reported medication use, and (8) CDC ME/CFS Symptom Inventory Grid Screener [25–28]. All patient data collected will be integrated into the clinical workflows to maximize the likelihood of consistent completion. To track and collect patient surveys, a registry will be created within CMIS which includes specific survey forms for each survey frequency. All surveys completed will be stored within EHR and accessible for participating clinicians to review. Surveys will be conducted via phone calls from FHCSD staff supporting LC&FIRP, with calls ranging from 30 to 90 min.

Each patient will be called a maximum of four times over the course of 4 weeks (once per week) to ensure the best possibility of achieving responses. Upon request, patients may request a copy of their survey responses. Patients who are unreachable for their 12-month survey or are unable to do the survey over the phone will be offered a shortened online version that includes the PROMIS-29 survey to be sent via text or email. An overview of the patient flow throughout the study can be seen in Fig. 2.

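### Unmasked clinicians may diagnose and refer patients after randomisation, and no stated step keeps patient identification or assignment independent of arm

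*Protocol article*

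**What the plan says.** All references are to the protocol article.

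- **Order of events.** Under Recruitment, enrollment, and study duration, clinicians consent, complete a baseline survey and are randomised; "Study enrollment commences upon randomization". Under Study design, "throughout participation, 856 FHCSD patients diagnosed with PCC, ME/CFS, or other PIFI will be assigned to the participating clinicians", and participation can last up to 37 months. Patients therefore enter after their clinician's arm is fixed.
- **Masking.** Under Randomization, allocation concealment, and blinding: "It is not possible to mask participating clinicians; however, their patients will have no knowledge of their potential participation". Data collectors and analysts are to stay blinded.
- **Route of entry.** Patients "may be referred to LC&FIRP by a participating clinician or by a non-participating clinician". Under Inclusion criteria, "FHCSD Primary Care Providers use CDC guidelines to diagnosis patients with PCC, ME/CFS, and or other PIFI before referring them to LC&FIRP". The same section describes two steps: referral to the programme, then assignment to a participating clinician. The assignment rule is not given.
- **Eligibility.** Adults with persistent symptoms and a decline in quality of life qualify. The categories include PCC without laboratory confirmation and an open class of other post-infectious illness. There are no exclusion criteria.
- **Baseline.** Under Patients, in Measures: "Upon assignment to a participating clinician participant, patients will be asked to share current demographic characteristics, symptoms, medical history, health history".
- **Analysis.** Patients are analysed by the arm of their assigned clinician. The model adjusts for the baseline measure and for measured characteristics found to be unbalanced.

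**The concern.** In a cluster trial, randomising clinicians protects the patient comparison only if the patients who enter do not depend on the arm. Here a participating clinician can make the diagnosis and the referral while knowing his or her own arm. Intervention clinicians also attend weekly teaching and case review on these same conditions, so they may come to recognise a different range of patients. The protocol itself allows for this kind of change. Under Researchers, the volume of PCC and ME/CFS cases is a measure of change in practice. Under Semi-structured interviews, clinicians and administrators are asked about change in patient panel composition.

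Two separate consequences could follow.

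- **Case mix.** If patients identified in one arm differ in unmeasured prognosis and remain in that arm, the 12-month difference in physical function is biased. The direction is unknown.
- **Exposure before baseline.** A patient already under an intervention clinician's care after teleECHO began may have had some benefit before the baseline survey. Adjusting for that baseline removes part of the effect. This costs power; it does not create false positives.

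**Working it through.** **1. The plan's own figures.** Inputs from Sample size: 300 evaluable patients per arm, 10 clinicians per arm with 30 patients each, ICC 0.1, d = 0.45 to 0.5, two-sided 5%.

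- Design effect = 1 + (30 − 1) × 0.1 = 3.9
- Effective n per arm = 300 / 3.9 = 76.9
- Standard error of the difference = √(2 / 76.9) = 0.161 SD
- Power (normal approximation) = 79.7% at d = 0.45 and 87.3% at d = 0.5

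The article gives 80.0% and 87%, so the figures reproduce. The power calculation is not in dispute; only its standard error is needed below.

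**2. Which stated safeguards reach the problem.**

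| Safeguard in the article | What it protects | What it leaves open |
|---|---|---|
| Concealed allocation of clinicians | Which arm a clinician gets | Which patients enter later |
| Patients unaware of their clinician's participation | Patient reporting | Selection by the clinician |
| Blinded data collectors and analysts | Measurement and analysis | Diagnosis and referral |
| CDC diagnostic guidelines | How a diagnosis is made | Who is recognised and referred |
| Adjustment for unbalanced measured characteristics | Measured differences | Unmeasured differences |

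None of them makes identification or assignment independent of arm.

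**3. Case mix: an illustration with assumed inputs.** Assume that participant-referred patients stay in the referrer's arm. Assume also that those identified in the intervention arm differ from those identified in the control arm by 0.2 SD in prognosis left after adjustment. Let s be the share of patients referred by participating clinicians. The document gives none of these values.

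Bias = s × 0.2 SD. Error rate = P(|Z + bias / 0.161| > 1.96).

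| s (assumed) | Bias (SD) | T-score points | Share of the 4.5-point target | Bias / SE | Error rate of a nominal 5% test |
|---|---|---|---|---|---|
| 10% | 0.02 | 0.2 | 4% | 0.12 | 5.2% |
| 25% | 0.05 | 0.5 | 11% | 0.31 | 6.1% |
| 50% | 0.10 | 1.0 | 22% | 0.62 | 9.5% |

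If assignment ignores who referred the patient, the expected bias from this source is zero whatever s is.

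**4. Exposure before baseline: conditional.** Let q be the share of intervention patients already exposed at baseline and f the fraction of the effect they already carry. The difference in change is multiplied by 1 − q × f.

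- q = 25%, f = 10%: factor 0.975; power 77.7% at d = 0.45
- q = 50%, f = 25%: factor 0.875; power 68.5% at d = 0.45
- q = 75%, f = 50%: factor 0.625; power 41.5% at d = 0.45

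These inputs are also assumed. The factor applies to a simple change score. With baseline as a covariate the loss is scaled by the regression slope on baseline, so it is smaller whenever that slope is below 1.

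**The case against.** The strongest objection is that a link is missing. Referral is to the programme, and assignment to a clinician is a second step. No section says that a referring clinician keeps the patient or chooses the arm. If assignment is independent of the referrer, selective referral by teleECHO clinicians spreads over both arms. A condensed article may leave the assignment rule to the full protocol. This stands. A reader might infer that participating clinicians enrol their own patients into their own arm, but the text does not show it.

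The training contrast is also smaller than it may seem. Both arms receive the monthly webinars and quarterly short courses, and the short courses consolidate findings from the weekly sessions. Common inclusion criteria, CDC guidelines and a system-wide instruction on the PCC code apply to everyone. So the contrast is an increment in training, and entry is not unconstrained merely because there are no exclusion criteria. This stands and limits the likely size.

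Third, about 200 clinicians are eligible and 20 take part, so roughly 180 potential referrers are outside the trial and the participating share may be small. A reader might take the 9.5% above as the trial's error rate. It is only the upper row of an assumed range.

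Lastly, a referral-source analysis is ordinary SAP content, and the SAP is not shown. Its absence from the article is no fault. What remains is the recruitment design that the article does state: unmasked clinicians, referral by them after randomisation, and safeguards that do not reach selection.

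**Conclusion.** The concern holds as a risk of identification bias, not as a demonstrated bias. The text establishes that clinicians know their arm, that they may diagnose and refer patients afterwards, that patient baseline is taken at assignment, and that no stated step separates identification or assignment from arm.

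Bias in the comparison also requires that participant-referred patients stay with the referrer's clinic panel or arm, which the article leaves unsaid. Direction and size cannot be determined. Under the assumed 0.2 SD difference and shares of 10% to 50%, the error rate of a nominal 5% test lies between about 5.2% and 9.5%.

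A reader might also infer that the baseline is generally contaminated. The text supports that possibility only for patients already under an intervention clinician's care after teleECHO began, and the article does not say how many there are. For them the consequence is a diluted effect.

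**What to change.** 1. Record referral source (participating or non-participating clinician) and referral date for every patient, from the EHR where available. While analysts are still blinded, pre-specify a supportive 12-month analysis restricted to patients referred by non-participating clinicians. Tabulate referrals and baseline characteristics by arm and source. Do not rely on referral source as a covariate to remove the bias: it is determined after randomisation and may itself depend on arm.
2. For patients still to be enrolled, assign non-participant referrals to clinicians by a central concealed sequence. The restricted analysis is clean only to the extent that assignment did not depend on arm, so report how earlier patients were assigned. Recruitment began in November 2021 and completion is estimated for January 2025. With 12 months of follow-up, entry must largely end by about January 2024, so this step reaches only later enrolments.

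**Cost.** One extra field and one extra, less precise model. If half the patients were excluded evenly across clinicians, each cluster would have 15. The design effect would be 1 + 14 × 0.1 = 2.4, the effective n per arm 150 / 2.4 = 62.5, and the standard error √(2 / 62.5) = 0.179 SD instead of 0.161. The loss is modest because clustering already limits the precision.
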